## 7.2 Laboratory Tests:

### 7.2.1 Hematology:

The following will be done at the Second Screening Visit (days -90 to -5) and on Immunization Phase Day 28 (± 3 days; Follow-up Visit Three), and if clinically indicated to evaluate illness during challenge.

 Hematocrit

 Hemoglobin

 White blood cell count and differential

 Platelet count

### 7.2.2 Clinical Chemistry:

The following will be done at the Second Screening Visit (days -90 to -5) and on Immunization Phase Day 28 (± 3 days; Follow-up Visit Three), and if clinically indicated to evaluate illness during challenge.

 ALT and AST

 Blood urea nitrogen and Creatinine

### 7.2.3 Clinical Laboratory Serologies:

The following serum determinations will be done at the Second Screening Visit:

 Anti-HIV antibodies

### Urinalysis:

The following analytes will be recorded at the Second Screening Visit (days -90 to -5) and on Immunization Phase Day 28 (± 3 days; Follow-up Visit Three), and if clinically indicated to evaluate illness during challenge.

- Glucose, Protein, and Hemoglobin
- **Drugs of abuse screening (second screening visit only)**

Any sample with any positive glucose, or any protein or hemoglobin > trace, will trigger performance of a complete urinalysis, including microscopic examination.

### 7.2.5 Pregnancy Testing:

Urine b-HCG determination will be performed on a freshly-obtained urine specimen on the day of each test article dose and on the day of challenge dosing on each female subject not having a verifiable history of hysterectomy. A negative result must be obtained and recorded before any test article or challenge inoculum is administered.

### 7.2.6 Specific Immune Response Assays :

 Serum will be obtained for influenza-specific special serologies (serum hemagglutination-inhibition titers) at the First Screening Visit (A/Panama/2007/99 only), at the Immunization Phase Day 0 visit (all three strains tested for this and subsequent samples), and on Immunization Phase Day**,** 28 (± 3), Challenge Phase Day 0, and Challenge Phase Day 20 - 30.Should hemagglutination-inhibition prove unworkable for the influenza B virus component, single radial hemolysis assay may be utilized.

- Nasal washes for influenza-specific secretory IgA by ELISA will be obtained at the Second Screening Visit (all three strains tested for this and subsequent samples), and on Immunization Phase Day**,** 28 (± 3), Challenge Phase Day 0, and Challenge Phase Day 20 - 30.
- Whole blood will be obtained for *in vitro* cytokine stimulation studies on Immunization Phase Day 0 and Immunization Phase Day28 (± 3).

### 7.2.7 Influenza Virus Detection:

- **On Challenge Phase Day 2 PRIOR to challenge, a throat swab will be obtained for detection and or quantitation of influenza virus using culture, antigen detection and / or molecular biology techniques.**
- **From Challenge Phase Day 3 to Challenge Phase Day 9, a nasal wash and throat swab will be obtained daily from each subject for detection and / or quantitation of influenza virus using culture, antigen detection and / or molecular biology techniques.**

## 7.3 Other Measurements:

### 7.3.1 History and Physical Examination:

A complete physical examination and medical history/review of systems will be performed and recorded before the first test article dose. Vital signs will be included in all complete physical examinations. Significant abnormalities in the physical examination will be recorded on the case report forms. The medical history should record significant problems active at the time of screening or within the last year. Problems which have been inactive within the last year, but which might alter the subject’s current or future management, should also be noted (e.g., known mitral valve prolapse, history of seizure disorder, etc.) The physical examination will be repeated as needed for evaluation of complaints during the trial, and a complete physical examination will be repeated prior to challenge. A third complete examination will be performed on Challenge Phase Day 8 or 9 prior to discharge from the isolation facility. Additional repeat examinations will be performed at the Challenge Phase Day 20 -30 visit only as necessary to evaluate any new complaints. Any new and clinically-significant abnormalities will be recorded as adverse events.

### 7.3.2 Brief, Directed Physical Examination after Treatments:

A brief, directed physical examination will be performed on Immunization Phase Days 0, 7, 14 and 21 to ensure eligibility for treatment (0 and 14) and to evaluate the presence of objective findings of vaccine reactogenicity (7 and 21). This examination will encompass the ears, nose, throat, and cervical lymph nodes, and will be recorded using a standardized worksheet (Appendix C). It is emphasized to site staff that continuity of observer for any given subject is important for these examinations and should be maintained if at all practicable.

### 7.3.3 Temperature Measurements During the Challenge Phase:

From Challenge Phase Day 1 to Day 9, oral temperature will be recorded at least four (4) times daily. Because these readings are critical to definitions of illness and to symptomatic and specific therapy criteria, temperatures of ≥ 37.6ºC must be confirmed by a repeat measurement not less than 20 minutes and not more than 60 minutes after the first reading. Subjects will be instructed not to eat or drink during the interval between the two measurements.

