Safety and immunogenicity data continue to be analyzed, but are in general consistent with prior experience. Approximately 70% of both one- and two-dose vaccinees had signficant aserum HAI responses. A per-protocol analysis of the challenge study data revealed influenza-like illness in 66.7% of challenged placebo recipients, 62.5% of challenged one-dose recipients (6.3% efficacy), and 31.8% of challenged two-dose recipients (52.3% efficacy); yielding a chi2 p value of 0.041 for the 3 x 2 table and a p value of 0.021 for trend with number of vaccine doses. However, examination of the data has revealed that physician exam findings were non-contributory with one exception: pharyngitis; and that the definition of pharyngitis as applied by the study physicians led to fulfillment of the criteria for “illness” in a number of essentially asymptomatic subjects. In addition, the calibration of the disposable digital thermometers used to monitor temperature was questioned, as these yielded mean baseline temperatures just over 36ºC. Setting aside physician-observed pharyngitis and using a definition of fever based on the baseline mean + three standard deviations revealed a similar, but much stronger, efficacy trend in the data: 57.1% illness in placebo recipients; 45.8% illness in one-dose recipients (19.8% efficacy); and 4.5% illness (92.1% efficacy) in two-dose recipients (chi2 p value of 0.0007 for the 3 x 2 table and a p value of 0.0003 for trend with number of vaccine doses). An analysis based on laboratory-confirmed influenza illness (which requires illness and either isolation of influenza virus or a four-fold rise in reciprocal HAI titer across the challenge interval) demonstrates 65% efficacy in the one-dose group and 100% in the two-dose group. Because the sensitivity of influenza culture has proved poor for this strain however, this analysis remains preliminary pending data from molecular detection methods and immunoflouresence studies.

The current study is being undertaken to: a) confirm the efficacy of the two-dose regimen at a 30 μg dose level, b) re-examine the efficacy of the one-dose regimen at the 30 μg dose level with refined illness criteria, and c) examine the possible efficacy of a two-dose regimen at a 15 μg dose level, which is also highly immunogenic.

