## 9.3 Illness Definitions and Analysis for Challenge Component:

9.3.1 Fever:

Fever will be defined as any oral temperature 37.9C which is confirmed by a repeat observation at an interval of not less than 20 minutes and not more than 60 minutes. Prior experience has shown that electronic digital thermometers used in climate-controlled environments may not precisely reflect the normal oral temperature range established in the era of mercury bulb instruments used in ambient conditions. Accordingly, an alternative definition of fever, i.e., ≥ 3 standard deviations above the mean of the third temperature observation on **Challenge** Phase Day 1, will be utilized if significantly lower than 37.9º C.

9.3.2 Upper Respiratory Illness:

A subject will be considered to have upper respiratory illness if he or she has any one of the following on two (2) consecutive days, at least one (1) day of which must feature grade 2 severity, or if any of the following attain grade 3 severity once:

- Self-reported symptoms:
  - Rhinorrhea (runny nose), or
  - Nasal congestion (stuffy nose), or
  - Sore throat.
- Physician findings:
  - Nasal discharge
  - Otitis
  - Sinus tenderness
  - Pharyngitis

9.3.3 Lower Respiratory Illness:

A subject will be considered to have upper respiratory illness if he or she has any one of the following on two (2) consecutive days, at least one (1) day of which must attain grade 2 severity, or if any of the following attain grade 3 severity once:

- Self-reported symptoms:
  - Cough, or
- Physician findings:
  - New wheezing, rhonchi, râles, or signs of consolidation

9.3.4 Systemic Illness:

A subject will be considered to have upper respiratory illness if he or she has any one of the following on two (2) consecutive days, at least one (1) day of which must attain grade 2 severity, or if any of the following attain grade 3 severity once:

- Headache
- Myalgia and/or athralgia

9.3.5 Illness (Any):

A subject will be considered to have illness if he/she fulfills the criteria for fever, or upper respiratory illness, or lower respiratory illness, or systemic illness or any combination thereof.

9.3.6 Infection:

A subject will be deemed to be infected if he/she has any one of:

- Influenza virus shedding in nasal wash at any level, or
- Detection of influenza virus in the throat swab by using **culture, antigen detection or** molecular biology techniques, or

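### Section 7.3.3 controls food and drink only between a raised temperature and its repeat, so the scheduled challenge-phase readings, including the Day 1 reading that sets the alternative fever cut-off, have no intake control

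*Protocol*

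**What the plan says.** Protocol 7.3.3 sets the frequency: "From Challenge Phase Day 1 to Day 9, oral temperature will be recorded at least four (4) times daily". It explains why care is needed: "Because these readings are critical to definitions of illness and to symptomatic and specific therapy criteria". A reading of 37.6ºC or more "must be confirmed by a repeat measurement not less than 20 minutes and not more than 60 minutes after the first reading", and for that interval only: "Subjects will be instructed not to eat or drink during the interval between the two measurements".

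Protocol 9.3.1 defines fever as an oral temperature at the 37.9ºC threshold "which is confirmed by a repeat observation at an interval of not less than 20 minutes and not more than 60 minutes". It adds an alternative cut-off, "≥ 3 standard deviations above the mean of the third temperature observation on" Challenge Phase Day 1, which "will be utilized if significantly lower than 37.9º C". The background in section 1.0 explains why an alternative was wanted. Thermometer calibration was questioned in the preceding challenge study, because "these yielded mean baseline temperatures just over 36ºC".

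Fever is one of the six binary clinical outcomes in 9.3.8.2. Under 9.3.5 it is enough on its own to classify a subject as ill.

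**The concern.** The restriction shows that the authors regard eating and drinking as able to distort an oral reading. Yet it protects only the second reading, and a second reading is required only when the first has already reached 37.6ºC. The first reading decides whether anything further happens, and it is unprotected. A first reading pushed up past the trigger by a hot drink is likely to be exposed by the controlled repeat. A febrile reading pushed down below 37.6ºC by a cold drink is recorded as it stands.

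The alternative cut-off is exposed in two ways. It rests on one uncontrolled reading per subject, and its rule multiplies the standard deviation of that reading by three. It may also lie below 37.6ºC, where the repeat and its intake rule do not operate. At stake is the quality of a measurement that the protocol itself calls critical.

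**Working it through.** **Step 1. Where intake is controlled.** The other places that deal with challenge-phase temperatures are Protocol 5.2, 7.1.10 to 7.1.14, 9.3.1 and Appendix B Table B.2. None restricts intake before a scheduled reading. The sentence in 7.3.3 is the only rule.

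**Step 2. Lowering needed to escape the recheck.** The drop must exceed the true temperature minus 37.6ºC. For a true 37.9ºC that is more than 37.9 − 37.6 = 0.3ºC.

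**Step 3. Chance that a whole fever is missed.** Let p be the share of readings lowered enough and k the number of scheduled readings the fever spans. If readings are independent, the chance that all are lowered is p^k. The protocol gives no p, so a range is shown.

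| p (assumed) | k = 1 | k = 2 | k = 4 |
|---|---|---|---|
| 10% | 10% | 1% | 0.01% |
| 20% | 20% | 4% | 0.16% |
| 30% | 30% | 9% | 0.81% |

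The risk is essentially confined to fevers that span one or two readings.

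**Step 4. Where the alternative cut-off would lie.** Cut-off = mean + 3 × SD. The documents place the earlier baseline mean just over 36ºC and give no SD. Assume a mean of 36.2ºC:

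- SD 0.25: 36.2 + 0.75 = 36.95ºC
- SD 0.30: 36.2 + 0.90 = 37.10ºC
- SD 0.35: 36.2 + 1.05 = 37.25ºC
- SD 0.45: 36.2 + 1.35 = 37.55ºC

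The cut-off stays below the 37.6ºC trigger for any SD under (37.6 − 36.2) / 3 = 0.467ºC. Readings between the cut-off and 37.6ºC then have no required repeat. If confirmation is still needed under the alternative definition, no rule supplies it. If it is not, a single reading raised by a warm drink could count as fever.

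**Step 5. How intake moves the cut-off.** Suppose a share p of the Day 1 third readings is lowered by d. The mean falls by p × d and the SD becomes √(s² + p(1 − p)d²). With mean 36.2ºC and s = 0.35ºC (all values assumed):

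| p | d (ºC) | new SD | cut-off before | cut-off after | shift |
|---|---|---|---|---|---|
| 10% | 0.5 | 0.381 | 37.25 | 37.29 | +0.04 |
| 20% | 1.0 | 0.532 | 37.25 | 37.59 | +0.34 |
| 50% | 0.3 | 0.381 | 37.25 | 37.19 | −0.06 |
| 100% | 0.3 | 0.350 | 37.25 | 36.95 | −0.30 |

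Intake that differs between subjects widens the spread. Intake common to all, such as a shared meal, leaves the spread alone and moves the mean. The cut-off can therefore go either way.

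Across s = 0.25 to 0.35ºC with 10–20% lowered by 0.4–0.6ºC, lowering alone raises the cut-off by 0.02 to 0.17ºC. The ends are:

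- s = 0.35, 10% by 0.4: 3 × √(0.1225 + 0.0144) − 0.04 − 1.05 = 0.02
- s = 0.25, 20% by 0.6: 3 × √(0.0625 + 0.0576) − 0.12 − 0.75 = 0.17

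If some readings are also raised, the rise is larger. At s = 0.30ºC, with 20% lowered by 0.6 and 20% raised by 0.5:

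- mean = 36.2 − 0.12 + 0.10 = 36.18
- variance = 0.09 + 0.072 + 0.05 − 0.0004 = 0.2116, so SD = 0.46
- cut-off = 36.18 + 1.38 = 37.56ºC, still below the 37.6ºC trigger

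**The case against.** The strongest reply is that this is a matter of detail. Waiting after food or drink is routine practice, the subjects are in a staffed quarantine unit, and silence in the protocol does not show that readings are taken straight after a cold drink. That has some force, but 7.3.3 does not leave intake to routine practice. It writes a rule and attaches it to the repeat only.

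Three other replies stand. At least four readings a day, any one of which can lead to a confirmed fever, make it unlikely that a sustained fever is missed. A subject whose fever is missed may still be classed as ill through symptoms or examination findings. And in a randomised, double-blind comparison the error should be similar in every arm.

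Stronger readings are tempting, and the documents do not support them:

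- **That fevers will be missed.** The text only allows it, and Step 3 limits it mainly to brief fevers.
- **That the alternative cut-off is inflated.** Step 5 shows it can fall as well as rise.
- **That the cut-off would be driven up to 37.9ºC, so that the alternative drops out.** This needs a mean such as 36.6ºC together with readings shifted both ways: 36.6 − 0.02 + 1.38 = 37.96ºC at s = 0.30. The protocol reports a baseline just over 36ºC. At 36.2ºC the same shifts give 37.56ºC, and 37.66ºC at s = 0.35.

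Thermometer calibration is a separate matter from intake.

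**Conclusion.** The gap stands as a minor to moderate weakness in how the measurement is standardised. The intake rule does not cover the readings that decide whether a repeat is taken, nor the one that sets the alternative cut-off. If that cut-off falls below 37.6ºC, as a baseline like the preceding study's would imply, the safeguard does not reach the readings that matter.

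The wording establishes the gap, but its size cannot be established. The protocol gives no SD, no intake effect, no meal times and no clock time for the third Day 1 reading. Every shift shown above rests on assumed values, and the miss probabilities also assume independent readings. The consequence to expect is added noise and some loss of sensitivity for fever in all arms. Neither bias between arms nor a measurable loss of power for any illness has been shown.

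**What to change.** Amend Protocol 7.3.3 so that subjects do not eat or drink for at least 20 minutes before every scheduled challenge-phase temperature, naming the third reading on Challenge Phase Day 1, as well as between a reading and its repeat. Twenty minutes is the protocol's own minimum interval between the two readings, so no new figure is introduced.

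The cost is one sentence, a staff instruction, and a short wait before four readings a day in an inpatient unit. The change must be in place before Challenge Phase Day 1, because that pre-challenge reading cannot be retaken once subjects have been inoculated. It brings readings below 37.6ºC under intake control but adds no repeat for them.

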### 7.3.4 Directed Physical Examination During the Challenge Phase:

A directed physical examination, including pulse and blood pressure, will be performed and recorded on every dayfrom Challenge Phase Day 1 to Day 9in accordance with the Challenge Physical Examination Worksheet (see Appendix G). The physician investigator may, at his/her judgement, perform any additional vital signs or physical examination necessary to evaluate or manage clinical illness. It is emphasized to site staff that continuity of observer is again desirable and should be maintained if at all practicable.

### 7.3.5 Concomitant Medications:

Subjects should be instructed not to introduce new medications without consulting or notifying the investigator or his designee. Subjects will be questioned regarding new medications at each visit through Challenge Phase Day 20 – 30 (Final Follow-up Visit) and any such medications recorded on the case report form.

## 7.4 Early Discontinuation:

Every reasonable effort should be made to ensure that each subject complies with the protocol and completes all study visits. However, a subject may withdraw or be withdrawn from participation if:

 The subject withdraws consent,

- The investigator recommends discontinuation in the interest of the subject’s safety or because of significant and irremediable protocol non-compliance,

 ID Biomedical, the ethics committee, or the MCA terminates the clinical trial.

Subjects must be stringently counseled that early withdrawal from the challenge isolation portion of the trial will be strongly discouraged, as it poses a risk both to the subject and to his/her contacts. Any subject insisting on early withdrawal during challenge isolation will be started immediately on a five (5) day course of oseltamivir (or amantidine), and will be encouraged to remain in the isolation unit as long as possible.

A complete Challenge Phase Day 20 – 30 (Final Follow-up Visit) evaluation and Study Termination case report form should be completed on any subject prematurely withdrawn from the clinical trial. No subject prematurely withdrawing/withdrawn will be replaced.

# 8.0 Immediate Complaints, Vaccine Reactogenicity, Findings of Influenza and Adverse Events:

## Immediate Complaints:

A selection of immediate complaints reasonably anticipated to occur as a result of receipt of the test articles is provided as a questionnaire (Appendix E) to be completed approximately 30 minutes after each test article dose and transcribed to the case report forms. The data will be reported as immediate complaints and presumed to be related to the test article. *These findings should NOT be additionally recorded as adverse events (see below) unless they fulfill the criteria set forth in section 8.4.1.*

## 8.2 Vaccine Reactogenicity:

A selection of subjective complaints reasonably anticipated to occur as a result of receipt of the test articles are provided in the Memory Aid (see sample in Appendix D), and a selection of potential physical findings also reasonably anticipated to occur as a result of receipt of the test articles are provided on the Brief Examination Worksheet (Appendix C) to be used on Immunization Phase Days 0, 7, 14, 21 and at any time during the seven days after each dose that a subject has grade 2 or greater severity complaints. Findings from these two sources will be recorded on the case report forms, reported as vaccine reactogenicity, and presumed to be related to the test article(s). *These findings should NOT be additionally recorded as adverse events (see below) unless they fulfill the criteria set forth in section 8.4.1.*

Definitions used to grade reactogenicity events are included as an integral part of each Brief Examination Worksheet (Appendix C) and Memory Aid page (Appendix D).

8.3 Symptoms and Findings of Influenza:

During the challenge period (Challenge Phase Days 1 – 9), symptoms and signs of influenza will be collected using the Influenza Symptom Diary Card (see Appendix F) and the Challenge Physical Examination Worksheet (see Appendix G) and their integral definitions. During this interval, findings captured by these two tools will be presumed to represent influenza consequent to challenge, and *will not be additionally captured as adverse events (see below) unless they fulfill the criteria set forth in section 8.4.1.*

## 8.4 Adverse Events:

An adverse event (AE) is any unfavorable, harmful, or pathologic change in a research subject as indicated by physical signs, symptoms and/or clinically significant laboratory abnormalities that occurs in association with the use of a product (trial-related), whether or not considered to be product-related. This includes intercurrent illnesses, injuries, worsening of pre-existing conditions, and events occurring as a result of product abuse or overdose. Stable pre-existing conditions and/or elective procedures to address them are not adverse events. Clinical laboratory findings are considered to be adverse events if regarded as clinically significant by the investigator, or if these cause (or should have caused) a change in the investigational drug regimen, a further diagnostic evaluation, or institution of any therapy.

All events fulfilling any part of the AE definition must be recorded on the adverse event case report form (with the exception of pre-defined immediate complaints or symptoms/signs of vaccine reactogenicity in the first seven [7] days following immunizations, and pre-defined symptoms and signs of influenza during the challenge (Challenge Phase Days 2 – 9); see sections 8.1, 8.2, 8.3, and 8.4.1).

Treatments and procedures are not adverse events; rather, the illness which precipitates them should be recorded. For example, “cholecystectomy,” is not an AE, but the diagnosis of “cholecystitis” or “gall stones” leading to the surgical (or medical) treatment is an AE. Where possible, specific diagnoses are preferred in reporting AEs. Individual complaints or findings may be reported as AEs, but when multiple complaints or findings occur together and can be logically and defensibly assembled into a single clinical syndrome or diagnosis, the latter is preferred. For example, an isolated finding of elevated AST and ALT would be recorded as “elevated transaminases.” If accompanied by fever, anorexia, nausea, and jaundice, however; a report of “hepatitis” would be preferable to a list of individual findings. If the new presence of HBsAg is also found, a more specific diagnosis of “hepatitis B” would be recorded.

